We believe a Student's t distribution is most closely represent our data. We anticipated that a 2-tailed statistical model is most appropriate. We found that the standard deviation for Hemoglobin A1C would be approximately 0.5% with a mean of 5.0 in normal subjects. We assume that most clinicians will consider a difference in Hemoglobin A1c of 0.3% to be clinically important. We wish to limit the Type I error rate to 0.05 or less and to achieve a power of at least 90% (i.e. a Type II error rate of 0.1). We chose the Hemoglobin A1C measurement to model this sample size estimation. Since we are planning on evaluating a total of 8 biochemical markers and survey instruments (HgA1C, lipid panel, BMI, BP, and PAM scores) we employed the Bonferroni inequality to adjust the Type I error rate. Under these assumptions, we calculate that approximately 60 participants are required. We proposed to collect an additional 6 participants in case non-parametric analysis seems appropriate.

CHR made home visits once a month to check on the participants' progress and reinforce the ideas presented in the classes. Six months after the class, the baseline lab work and clinical measurements repeated. Participants also repeated the PAM questionnaire. We hypothesize that the participants' HgA1C, lipid panel (total cholesterol, HDL, LDL, triglycerides), BMI, BP, and PAM scores will have improved from their baseline numbers taken before the education course and follow up with a CHR.

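### The required sample size of about 60 does not follow from the protocol's stated inputs once the Bonferroni adjustment is applied, and the input that decides power at 60 is not stated

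*Protocol*

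**What the plan says.** The only sample-size justification is one paragraph in the Methods section of the Protocol. HbA1c is the modelling variable, with a Student's t model. The inputs are:

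- Sidedness: "We anticipated that a 2-tailed statistical model is most appropriate".
- Variability: "the standard deviation for Hemoglobin A1C would be approximately 0.5% with a mean of 5.0 in normal subjects".
- Effect: "a difference in Hemoglobin A1c of 0.3% to be clinically important".
- Error rates: an overall type I error of at most 0.05 and "a power of at least 90% (i.e. a Type II error rate of 0.1").
- Multiplicity: "we are planning on evaluating a total of 8 biochemical markers and survey instruments (HgA1C, lipid panel, BMI, BP, and PAM scores"), and for that reason "we employed the Bonferroni inequality to adjust the Type I error rate".

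The paragraph concludes: "Under these assumptions, we calculate that approximately 60 participants are required". Six more participants are proposed in case a non-parametric analysis is used, making 66. The Possible Difficulties section repeats 60 as the number needed.

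The paragraph does not give the per-test alpha or the formula, and it does not say whether the test is paired or two-sample. The SD is described as that of HbA1c in normal subjects; nothing calls it an SD of change. The summary at the front of the Protocol gives one arm, and the hypothesis in the Methods section is improvement from each participant's own baseline at six months.

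**The concern.** The conclusion claims to rest on all the listed assumptions together, including the multiplicity adjustment and 90% power. If the number comes from a calculation that omits one of them, the paragraph promises a combination of error control and power that has not been shown. A reader would then take a non-significant HbA1c result as coming from a study with 90% power at the adjusted level, when the document does not establish that. The design adds to the difficulty. In a one-arm before-after study, precision depends on the SD of the within-person change, which is not given.

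**Working it through.** **Inputs** (all from the Methods paragraph): difference δ = 0.3; SD = 0.5; two-sided; power 0.90; 8 outcomes. Derived per-test alpha: 0.05/8 = 0.00625.

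**Formulas** (normal approximation; the results quoted elsewhere use the exact noncentral t, which is slightly larger):

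- Paired: n = [SD_change × (z_α + z_β)/δ]².
- Two independent groups: n per group = 2 × [SD × (z_α + z_β)/δ]².
- If 0.5 is a between-person SD at each visit and ρ is the baseline-to-6-month correlation: SD_change = 0.5 × √(2(1 − ρ)).

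**Step 1: attempt to reproduce 60 with the adjustment.** z_α = 2.734 and z_β = 1.282, so (z_α + z_β)² ≈ 16.13.

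- Paired, SD_change 0.5: (0.5/0.3)² × 16.13 = 2.778 × 16.13 = 44.8, so 45 (49 by t).
- Paired, ρ = 0, SD_change = 0.5 × √2 = 0.707: 5.556 × 16.13 = 89.6, so 90 (94 by t).
- Two-sample: 2 × 2.778 × 16.13 = 89.6, so 90 per group (92 by t).

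None of these is near 60. Counting the outcomes differently does not help. For every Bonferroni divisor from 2 to 12, the t-test results run over 38–52, 72–100 and 71–98 per group for the three cases.

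**Step 2: the same without the adjustment.** z_α = 1.960, so (z_α + z_β)² ≈ 10.51.

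- Paired, SD_change 0.5: 2.778 × 10.51 = 29.2, so 30 (32 by t).
- Paired, ρ = 0: 5.556 × 10.51 = 58.4, so 59 (61 by t).
- Two-sample: 58.4, so 59 per group (60 by t; power at 60 per group is 90.3%).

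| Reading of the inputs (t-test, 90% power) | α = 0.00625 | α = 0.05 |
|---|---|---|
| Paired, 0.5 is the SD of change | 49 | 32 |
| Paired, 0.5 is between-person, ρ = 0 | 94 | 61 |
| Two independent groups, per group | 92 | 60 |

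At the stated power and sidedness, a figure near 60 appears only in the right-hand column.

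**Step 3: what 60 delivers in the actual design.** Paired t-test at α = 0.00625, with 0.5 as a between-person SD. The correlation is not in the Protocol, so the range below is an assumption.

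| ρ | SD of change | n for 90% | Power at 60 |
|---|---|---|---|
| 0 | 0.707 | 94 | 67% |
| 0.3 | 0.592 | 67 | 86% |
| 0.38 | 0.557 | 60 | 90% |
| 0.5 | 0.500 | 49 | 96% |
| 0.7 | 0.387 | 31 | >99% |

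The largest SD of change that still gives 90% power at 60 is about 0.56. With a between-person SD of 0.5 this means ρ ≥ 1 − 0.56²/(2 × 0.5²) = 1 − 0.3136/0.5 ≈ 0.37. If 0.5 is itself the SD of change, the ρ = 0.5 row applies: 49 suffice, and 60 gives 96%. With all 66 participants, power at ρ = 0 rises only to 73%, while a correlation of about 0.31 is enough for 90%.

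**The case against.** The strongest reply is that 60 may be ample. Repeat HbA1c values on the same people need not be uncorrelated, and zero is the least favourable non-negative value. With a correlation of 0.5, or with 0.5 read as the SD of change, 60 exceeds the Bonferroni requirement of 49. This stands. A reader might infer from the mismatch that the study is underpowered and that its true power is 67%. The Protocol does not support that, because the 67% rests on a zero correlation that it never states. The same reply does not rescue the stated number, however, since the favourable reading gives 49, not 60.

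A second reply is that the origin of 60 is unknown. This also stands. No formula is named, and a numerical match is not proof. Other routes come close: a paired t-test at 0.00625 with an SD of change of 0.5 and 95% power needs 58, and an SD of change of about 0.56 at 90% power needs 60. The first uses a power different from the 90% printed as a type II error of 0.1, and the second uses an SD that appears nowhere. A reader might state as fact that the adjustment was never applied. The match suggests it but cannot establish it.

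A third reply is that HbA1c is a secondary outcome, PAM being primary, and that Bonferroni is mentioned only within the sample-size argument. Both are true. The point is therefore about the sample-size statement, and the Protocol cannot be said to commit every final test to 0.00625. But the Protocol chose HbA1c as the basis for its sample size, and the inputs and result it prints do not agree.

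**Conclusion.** The point holds as a failure to reproduce. With the stated SD, difference, sidedness, power and Bonferroni adjustment for 8 outcomes, the required number is 49, 94 or 92 per group depending on how the SD and test are read. It is not about 60. The figure agrees only with an unadjusted 0.05, most exactly as 60 per group in a two-sample comparison that a one-arm study does not have.

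Whether 60 gives 90% power at 0.00625 cannot be settled from the document. It does if the SD of the 6-month change is at most about 0.56, and it does not if that SD is larger. Over correlations from 0 to 0.5 the power runs from 67% to 96%. That range takes 0.5 as the between-person SD, a value from normal subjects with a mean of 5.0, while the eligibility criterion asks for HbA1c of 6.6% and above. The 0.5 therefore needs its own justification for this population.

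**What to change.** Replace the sample-size sentence with a paired (one-sample) calculation on the 6-month change in HbA1c. It should:

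- name the test and print the per-test alpha actually used for HbA1c;
- give a justified SD of within-person change, or a between-person SD with an assumed correlation, appropriate to participants with diabetes;
- show the power at 60 over a range of SD of change or correlation, in the form of the last table above, and not as a single 90% or a single 67%;
- drop the claim that 60 follows from the Bonferroni-adjusted inputs, unless the restated calculation supports it.

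The cost is one rewritten paragraph and possibly a less favourable stated power. No participants need be added.

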## **Possible Difficulties**

One potential difficulty will be recruiting enough participants to participate in the classes. We need 60 participants for a statistical analysis from the relatively small community. We plan to reach our recruitment goal by advertising the classes to the community through radio announcements and fliers, as well as contacting past participants from the ZKP that qualify for inclusion in this study.

Language may also be a potential barrier in this study. The classes will be conducted in English. Approximately 90% of Zuni's speak a language other than English at home. Although most

of the people of Zuni know English, some of the elderly may not be fluent in English or may prefer to communicate in their native tongue. For this reason, local CHR will be present at all of the classes and will be available to translate to any participant that is not comfortable speaking in English.

## **Limitations and Biases**

One limitation of our study may be its focus on diabetes, versus other illnesses. However, we believe that by developing a targeted approach as described within the small, indigenous Zuni population will be highly scalable for future efforts against other chronic conditions.

Furthermore, we cannot account for patient attrition that may result over the course of our study. With a relatively small cohort, it is crucial that we maintain a high retention rate for the various aspects of the study, in order to generate statistically-significant results.

One of the strengths of this study is its singular, culturally-sensitive approach to the Zuni people. Presumably, this may limit our future ability to translate the curriculum for other populations.

## Pragmatic Trial of Educational Intervention

[figure not shown]

Supplement: S1 Protocol — (PDF) [file pone.0125820.s002.pdf]
